**Methods:**

LOOPS is a prospective, multicenter observational biomarker trial recruiting 100 patients with mCRPC eligible for PSMA RLT across 3 Bavarian cancer research centers in Germany. Patients will undergo up to 6 cycles of [^177^Lu]Lu-PSMA-617. Blood samples for ctDNA analysis will be collected longitudinally (at baseline and after cycles 1, 2, 4, and 6) and processed according to standardized protocols. Imaging with PSMA positron emission tomography–computed tomography and clinical and biochemical data will be systematically collected. The primary end points are the prognostic and predictive value of baseline ctDNA for treatment response, defined by imaging- and prostate-specific antigen (PSA)–based response criteria after 2 cycles of PSMA RLT. Predictive performance will be evaluated using receiver operating characteristic analyses, including the determination of optimal ctDNA cutoffs, sensitivity, specificity, positive and negative predictive values, and multivariable logistic regression models adjusting for relevant clinical confounders. Secondary end points assess the concordance and correlation between ctDNA dynamics, systematically assessed PSMA positron emission tomography–computed tomography response, and PSA changes, as well as associations between ctDNA and clinical or laboratory (eg, age, Gleason score, and other) characteristics at baseline and during follow-up. Exploratory analyses will investigate early molecular response patterns based on short-term ctDNA changes and will characterize clonal dynamics and potential resistance mechanisms under therapy.

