### Outcomes

Two coprimary outcomes are specified. The first is the prognostic value of baseline ctDNA for nonprogression after 2 cycles, as assessed by PSA response according to PCWG3 (Prostate Cancer Clinical Trials Working Group 3) criteria [19]) and by RECIP 1.0 (Response Evaluation Criteria in PSMA-imaging, version 1.0) [20,21] defined as partial response or stable disease vs progression. The second is the concordance between ctDNA dynamics (percent change from baseline) and imaging-based response according to RECIP 1.0, as well as PSA response, after cycles 2, 4, and 6. Secondary outcomes examine associations between baseline ctDNA features and clinical or laboratory parameters (eg, age, Gleason score, PSA, alkaline phosphatase, lactate dehydrogenase, and metastatic distribution) and relate longitudinal ctDNA changes to clinical and laboratory trajectories. Exploratory outcomes include a very early molecular response defined a priori as a ≥30% decline in ctDNA at 6 weeks after the first cycle and the characterization of clonal dynamics and resistance-associated alterations across multiple time points.

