### Sample Size

The planned sample size of 100 patients is based on a priori biometrical considerations and reflects expected feasibility in this population with advanced mCRPC. Due to disease severity and anticipated attrition, the primary end point (treatment response at first posttherapy restaging after 2 cycles of therapy) is expected to be evaluable in approximately 70 patients. On the basis of this effective sample size, power calculations demonstrate that clinically meaningful differences in response rates between patients with and without a ctDNA-based predictive marker or marker change can be detected with 80% power at a 2-sided significance level of α=.05. Specifically, depending on the prevalence of the marker or marker change (25%, 50%, or 75%), differences in response probabilities of 0.33 to 0.41 between marker-positive and marker-negative patients are detectable using Fisher exact test. These effect sizes correspond to sensitivities ranging from 38% to 88% and specificities from 44% to 93%, supporting the ability of the study to evaluate the prognostic and predictive performance of ctDNA metrics. Therefore, the planned sample size is considered adequate for the primary analyses while remaining consistent with the pragmatic, multicenter, observational design of the study. To control the family-wise error rate for the 2 coprimary end points, a hierarchical testing strategy will be applied. The association between baseline ctDNA and treatment response will first be tested at a 2-sided significance level of α=.05. Only if this test is statistically significant, the discriminative performance (receiver operating characteristic analysis and area under the curve) will be formally evaluated at the same α level.

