Treatment response is further assessed by analyzing longitudinal changes in ctDNA levels and their concordance with PSMA PET-CT and PSA responses, using the Cohen κ coefficient and correlation analyses. Secondary analyses investigate associations between baseline and longitudinal ctDNA metrics and clinical or laboratory parameters, including subgroup comparisons based on patient characteristics. Exploratory analyses focus on the identification of very early molecular responders based on short-term ctDNA changes and on the characterization of clonal evolution and potential resistance mechanisms using deep sequencing and computational clonal deconvolution methods. General statistical considerations include the handling of missing data, adjustment for multiple testing, and sensitivity analyses to ensure robustness of the results. Given that tumor burden and ctDNA levels may change over relatively short time intervals in heavily pretreated mCRPC, the temporal separation between baseline PSMA PET-CT imaging and baseline blood sampling will be accounted for in the statistical analysis. The exact interval (in days) between PET-CT and blood draw will be recorded for all patients. The primary analysis correlating baseline ctDNA with PET-derived tumor burden will be prespecified to include only patients with a PET-to-blood interval of ≤28 days. In addition, sensitivity analyses will be performed in the full cohort, incorporating the PET-to-blood interval as a covariate (modeled as a continuous variable and as a categorical variable ≤28 vs 29‐56 days). Patients with intervals exceeding 28 days will be described separately, and the impact of their inclusion vs exclusion on key estimates will be explicitly reported. Furthermore, we will assess the association between cumulative administered activity and longitudinal changes of ctDNA. Cumulative activity will be modeled as a continuous exposure variable and analyzed in relation to ctDNA dynamics using regression-based approaches. Landmark analyses will be used where appropriate to mitigate immortal time bias.

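### The hierarchy said to control error for the two coprimary end points has two steps that both belong to the first one; the concordance coprimary is in neither, and the sections disagree on its rank

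*Protocol article*

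**What the plan says.** All references are to the protocol article.

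- **Outcomes** names two coprimaries. "The first is the prognostic value of baseline ctDNA for nonprogression after 2 cycles", judged by PSA and by RECIP 1.0. "The second is the concordance between ctDNA dynamics (percent change from baseline) and imaging-based response according to RECIP 1.0", and also PSA response, after cycles 2, 4 and 6.
- **Sample Size** announces the error control: "To control the family-wise error rate for the 2 coprimary end points, a hierarchical testing strategy will be applied". Step 1: "The association between baseline ctDNA and treatment response will first be tested at a 2-sided significance level of α=.05". Step 2, only if step 1 is significant: "the discriminative performance (receiver operating characteristic analysis and area under the curve) will be formally evaluated at the same α level".
- **Abstract, Methods** gives a different ranking. "The primary end points are the prognostic and predictive value of baseline ctDNA for treatment response", while "Secondary end points assess the concordance and correlation between ctDNA dynamics", PET-CT response and PSA changes.
- **Statistical Methods** confines the primary analyses to baseline ctDNA and response after 2 cycles. It assigns Cohen's kappa and correlation to concordance, with no significance level, order or gate.

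**The concern.** A fixed-sequence procedure protects only the hypotheses in the sequence. Here the sequence is offered as protection for two named coprimaries, but one of them is not in it. A reader of the final report could not tell whether a concordance result is a confirmatory coprimary finding, a secondary one, or an estimate with no error control.

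Timing adds weight. Results reports 63 patients enrolled and liquid-biopsy analysis begun in January 2026, with recruitment due to finish in September 2026. If the rank of concordance is settled only after results are seen, that choice becomes post hoc.

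**Working it through.** **1. Match steps to end points.**

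| | Marker | Compared with | Step in Sample Size |
|---|---|---|---|
| Coprimary 1 (Outcomes) | baseline ctDNA | nonprogression after cycle 2 | step 1 (association) and step 2 (ROC/AUC) |
| Coprimary 2 (Outcomes) | change in ctDNA | RECIP 1.0 and PSA after cycles 2, 4, 6 | none |

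The hierarchy is consistent with the Abstract and with the opening of Statistical Methods, where only baseline ctDNA is primary. It is inconsistent with Outcomes.

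**2. What the sample size figure covers.** Inputs from Sample Size: about 70 evaluable patients, 2-sided α = .05, 80% power, Fisher exact test, prevalence of the marker or marker change 25%, 50% or 75%; stated detectable difference 0.33 to 0.41. The overall response rate r is not given, so 0.3 to 0.7 was assumed. With prevalence q and difference d, the response rates are p2 = r − q·d and p1 = p2 + d. Power is the sum of the binomial probabilities of all tables with Fisher P ≤ .05.

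- Example, 35 vs 35, r = 0.6, d = 0.35: p2 = 0.6 − 0.5 × 0.35 = 0.425, p1 = 0.775, power 0.806.
- Example, 53 vs 17, r = 0.6, d = 0.39: p2 = 0.6 − 0.757 × 0.39 = 0.305, p1 = 0.695, power 0.803.
- Over r = 0.3 to 0.7, the smallest d with 80% power is about 0.325 to 0.365 at 50% prevalence and 0.335 to 0.40 at 25% or 75%.

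The stated range is reproduced to within about 0.01. It concerns a difference in response rates at the first restaging, for a baseline marker or a marker change. It gives nothing on the size of kappa, or on cycles 4 and 6.

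**3. Family-wise error if concordance is tested outside the hierarchy.** Assume formal tests at .05, each able to succeed alone, independent of one another and of coprimary 1. With k concordance tests, the error is 1 − 0.95^(k+1), with upper bound 0.05(k+1).

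- k = 1: 1 − 0.95² = 0.0975 (bound 0.10).
- k = 3: 1 − 0.95⁴ = 0.185 (bound 0.20).
- k = 6 (2 references × 3 time points): 1 − 0.95⁷ = 0.302 (bound 0.35).

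Positive correlation lowers this. Simulated error for the six concordance tests alone is 0.162 at pairwise correlation 0.7. Adding an independent coprimary 1 gives 1 − (1 − 0.162) × 0.95 = 0.204.

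**4. Does step 2 add a hypothesis?** No AUC null is stated; take 0.5.

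- Two-category marker: AUC = (sensitivity + specificity)/2. This equals 0.5 exactly when the response rates in the two marker groups are equal, which is the step 1 null.
- Continuous marker (simulation, n = 70, 2,000 runs, 50% response assumed): the AUC test was significant in 99.8 to 100% of runs in which Mann-Whitney was. Where a logistic likelihood-ratio test was significant, the AUC test was too in 92 to 96% of runs under an effect and in 80% under the null.

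The second slot thus goes to nearly the same question as the first.

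**5. After repair.** With one concordance test as step 2, if the step 1 null is true an error requires rejecting it (at most .05); if it is false, only step 2 can err (at most .05). Family-wise error is at most .05. The detectable differences for step 1 do not change.

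**The case against.** The strongest reply is that Outcomes is the outlier. Association followed by discrimination fits the Abstract and Statistical Methods, and if concordance is secondary there is no coprimary for the hierarchy to miss. Kappa and correlation may also be meant as estimates. Statistical Methods promises adjustment for multiple testing, with detail perhaps in a statistical analysis plan that is not shown.

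Much of this stands: the root fault is a contradiction over rank, and inflation arises only if concordance is formally tested. It does not remove the point. Outcomes calls concordance coprimary, Sample Size claims control for two coprimaries, and a general promise of adjustment does not put concordance into a fully described two-step procedure.

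A reader might infer more than the article supports:

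- *That concordance has no power statement at all.* Sample Size does cover a marker change against response at the first restaging. For a two-by-two table, that is also a test of kappa = 0 at that visit.
- *That there is a third primary end point.* "The primary analysis correlating baseline ctDNA with PET-derived tumor burden will be prespecified" is contrasted with sensitivity analyses in the full cohort. This is the ordinary use of primary for the main analysis set (PET-to-blood interval up to 28 days).
- *That step 2 repeats step 1 exactly.* That needs a null of AUC = 0.5 and a binary-marker or rank test in step 1. Neither is fixed, and agreement with logistic regression is only close. Redundancy in a fixed sequence does not inflate error either.
- *That the AUC will be biased upward.* Only its formal evaluation is gated; Statistical Methods plans ROC analysis without a condition. Bias would arise only if the AUC were withheld when step 1 fails.
- *That the plan has a 30% false-positive rate.* The article states no six formal tests and no rule that any one suffices. If both coprimaries had to succeed, no inflation would arise, but the article does not state that rule and offers a hierarchy instead.

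**Conclusion.** Wrong as written, in a narrow and easily repaired way. The stated family-wise error control does not hold for the coprimaries as Outcomes defines them, and the Abstract, Outcomes, Sample Size and Statistical Methods do not agree on whether concordance is primary. This rests on the text alone.

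The size is conditional: about 0.10 with one ungated concordance test and up to about 0.30 with six, assuming formal tests at .05 and independence. It is zero if concordance is secondary or estimation only. That step 2 is nearly redundant assumes a null of AUC = 0.5. The detectable differences of 0.33 to 0.41 are not in dispute, but they do not support a claim of adequacy for the size of kappa or for cycles 4 and 6.

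**What to change.** Use one end point list in the Abstract, Outcomes, Sample Size and Statistical Methods, fixed before outcome data are analysed. Either:

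- make concordance secondary everywhere, as in the Abstract, and stop describing the hierarchy as covering two coprimaries; or
- keep it coprimary, make one prespecified concordance test step 2 at α = .05 after a significant step 1 (for example at the cycle-2 restaging, against one named reference), and rank all other concordance comparisons as secondary.

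Which of the two to take is the sponsor's choice. In either case, report the AUC with its 95% CI whatever the step 1 result, as an estimate and not a gated test. Limit the adequacy statement in Sample Size to the cycle-2 response comparisons that it powers.

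The cost is wording in the protocol and in any analysis plan and registry entry that carries the same list; no patients, samples or visits. The downside is that most concordance results, and under the first option all of them, lose coprimary status.

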### Recruitment

Eligible patients are identified during routine evaluation for PSMA RLT at participating centers. Study information is provided during treatment planning, and informed consent is obtained prior to baseline sampling.

### Data Collection Methods

#### Biospecimens and Preanalytical Procedures

Peripheral blood is collected in ethylenediaminetetraacetic acid tubes (5×9 mL at baseline and 3×9 mL at follow-up visits), processed within 2 hours, double-spun, aliquoted, and stored decentrally at −80 °C. Preanalytical procedures are harmonized across sites using standard operating procedures adapted from the Augsburg Longitudinal Plasma Study [17], with a barcode-based chain-of-custody. Matched leukocyte DNA is collected to facilitate the filtering of germline variants and clonal hematopoiesis.

#### ctDNA Workflow

Centralized analyses are performed at the Interdisciplinary Laboratory for Experimental Cancer Research, Augsburg. Cell-free DNA is extracted from approximately 4 mL of plasma and quantified with assessment of fragment size distribution. Libraries are prepared using the AVENIO ctDNA Surveillance V2 panel (197 genes, including National Comprehensive Cancer Network–listed prostate cancer genes with unique molecular identifiers for error suppression) and sequenced using paired-end 100 base pairs reads on an Illumina NovaSeq X to >20,000×raw coverage. Bioinformatics identifies single nucleotide variants or indels and copy number alterations; ctDNA burden is summarized as variant allele fractions and human genome equivalents. ΔctDNA is defined as the percent change from baseline at each on-treatment time point. Variants consistent with germline origin and clonal hematopoiesis (eg, *DNMT3A*, *TET2*, and *ASXL1*) are annotated and excluded from tumor-specific analyses. Clonal hematopoiesis of indeterminate potential (CHIP) refers to the age-related expansion of hematopoietic cell clones carrying recurrent somatic mutations (often in genes such as *DNMT3A*, *TET2*, and *ASXL1*) [1]. DNA from these CHIP-derived clones can be released into the bloodstream and detected in plasma, where such mutations may be mistakenly attributed to the tumor, potentially confounding ctDNA analysis. Therefore, filtering out CHIP-associated variants via matched leukocyte DNA sequencing is essential to avoid false-positive results and ensure that ctDNA findings truly reflect tumor-derived alterations. Prespecified quality metrics and reporting thresholds are applied uniformly.

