### Unmet Need

Despite these advances, response heterogeneity and the ability to predict response remain major challenges. Only approximately 50% of patients achieved an objective radiographic response in the VISION trial [4]. This discordance between high PSMA expression on positron emission tomography (PET)–computed tomography (CT) and limited efficacy suggests incompletely understood resistance mechanisms, including tumor microenvironment heterogeneity, insufficient radiation doses to micrometastases, and intrinsic molecular factors such as genetic alterations in DNA damage repair pathways [5,6]. Liquid biopsy (LBx) has emerged as a promising tool that enables longitudinal, minimally invasive monitoring while mitigating the sampling bias of single-site tissue biopsies [7]. LBx analytes include circulating tumor cells (CTCs), circulating tumor DNA (ctDNA), extracellular vesicles, and tumor-derived RNA [8]. Among these, ctDNA is particularly promising in mCRPC. First, it is detectable in a substantial majority of patients (approximately 76%‐94%), with lower detection in patients with limited disease burden or low prostate-specific antigen (PSA) levels [9-11]. Second, ctDNA levels strongly correlate with clinical outcomes, including PSA response, progression-free survival, and overall survival, as demonstrated in multiple studies, including the TheraP trial [12,13]. Third, ctDNA provides a comprehensive view of the tumor genomic landscape, enabling detection of actionable mutations at higher rates than CTC-based assays or single-site tissue biopsies [14]. Recent studies have demonstrated specific genomic alterations detectable in ctDNA that predict resistance to PSMA RLT, including amplifications of *FGFR1* and *CCNE1*, as well as *CDK12* mutations [15]. Additionally, genome-wide copy number variation analysis has shown that a higher burden of genomic instability correlates with poorer treatment response [16]. Finally, ctDNA has been shown to correlate with imaging-derived biomarkers such as PSMA-positive tumor volume on PET, with correlations being particularly strong in patients with castration-resistant cancer (*r*=0.65; *P*<.001) compared to hormone-sensitive patients [11]. In contrast, early LBx applications in PSMA RLT using CTCs showed limited predictive value [17] and a 20% false-negative rate for PSMA expression [18].

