### Limitations and Challenges

Several methodological challenges must be acknowledged. First, ctDNA detection is not uniform across all patients. Low-shedding tumors or those with limited tumor burden may yield false-negative results. Comparative studies have shown that ctDNA detection rates are significantly lower than PSMA PET detection rates, particularly in hormone-sensitive disease and at low PSA levels [11]. Although LOOPS uses sensitive sequencing and harmonized SOPs, residual variability in detection and quantification is unavoidable.

Second, ctDNA is a systemic signal and cannot localize alterations to specific lesions, potentially obscuring intrapatient heterogeneity evident on PET-CT. Consequently, lesion-restricted resistance mechanisms can be systemically diluted below detection thresholds. This underscores the value of integrating molecular and imaging biomarkers rather than privileging either alone.

Third, attrition is expected in an advanced disease cohort; although the analysis plan anticipates approximately 70 evaluable patients for the primary end point, small numbers in exploratory subgroups will limit power and mandate cautious interpretation with appropriate multiplicity control. However, experience from smaller pilot studies suggests that meaningful associations can be detected even in cohorts of 17 to 44 patients [15,16], providing confidence in the planned sample size.

Fourth, generalizability may be constrained by recruitment within 3 Bavarian academic centers and by variation in locally available PSMA-directed radiotracers; central reading and SOP harmonization mitigate, but do not eliminate, site-level heterogeneity.

Fifth, as an observational study embedded in routine care, LOOPS cannot establish causal effects or test treatment adaptation; early-change analyses will use landmarking to reduce immortal time bias; however, residual confounding may persist.

Sixth, posttherapeutic single-photon emission CT–based dosimetry is not included in the analysis. Although absorbed radiation dose is a biologically relevant determinant of treatment response and resistance, homogeneous dosimetric data are not available due to heterogeneous clinical imaging protocols across the participating centers and the current lack of standardized dosimetry methodologies.

Finally, despite paired leukocyte filtering, clonal hematopoiesis and preanalytical factors remain potential sources of noise.

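### ΔctDNA as percent change has no value when baseline ctDNA is undetectable, and the sample of about 70 makes no stated allowance for such patients

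*Protocol article*

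**What the plan says.** All references are to the protocol article.

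- **ctDNA Workflow** gives the scale, "ctDNA burden is summarized as variant allele fractions and human genome equivalents", and the change measure, ΔctDNA, which "is defined as the percent change from baseline at each on-treatment time point".
- **Outcomes** makes the concordance of this percent change with RECIP 1.0 and PSA response after cycles 2, 4 and 6 the second of two coprimary outcomes. (The Abstract lists concordance under the secondary end points.) An exploratory outcome uses the same scale: "a very early molecular response defined a priori as a ≥30% decline in ctDNA at 6 weeks after the first cycle".
- **Unmet Need** says of ctDNA in mCRPC that "it is detectable in a substantial majority of patients", with a cited range of about 76–94% and lower detection when disease burden or PSA is low.
- **Limitations and Challenges** concedes that "Low-shedding tumors or those with limited tumor burden may yield false-negative results".
- **Sample Size** reduces 100 patients to about 70 because of disease severity and attrition before restaging. It then states that "differences in response rates between patients with and without a ctDNA-based predictive marker or marker change can be detected with 80% power", using Fisher's exact test, for differences of 0.33 to 0.41 at marker prevalences of 25%, 50% or 75%.
- **Statistical Methods** analyses concordance with Cohen's κ and correlation. It announces missing-data handling and sensitivity analyses without giving a rule.

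**The concern.** The difficulty is in the definition the article states, not in something it leaves out. If no tumour variant is found at baseline, the denominator is zero and ΔctDNA does not exist. If only a few mutant molecules are found, the ratio is dominated by sampling error.

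Two groups are affected. The first is patients with low burden, where the article itself expects lower detection, so any loss would be selective. The second, within the first, is patients who go from undetectable to detectable on treatment. That pattern is molecular progression and belongs to the study's stated interest in resistance, but the metric cannot record it.

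At stake are who contributes to a coprimary concordance analysis and to the early-response outcome, and how many patients stand behind the power claimed for a marker change. An undetectable baseline is a measured result, so a general promise to handle missing data does not clearly cover it.

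**Working it through.** **1. Inputs.** About 70 response-evaluable patients, two-sided α = 0.05, Fisher's exact test, prevalences 25/50/75% and differences 0.33–0.41 (Sample Size). Detection 76–94% (Unmet Need; cited studies, not this assay). The overall response rate is not stated.

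**2. The plan's own power figure.** With prevalence π, response probabilities p1 (marker-positive) and p2 (marker-negative), and overall response r = πp1 + (1−π)p2:
- sensitivity = πp1 / r
- specificity = (1−π)(1−p2) / (1−r)

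Solving back from the stated sensitivities and specificities gives r of about 0.58–0.59, so r ≈ 0.6 is assumed. At n = 70 a doubled-tail Fisher test then has 80% power for differences of 0.38, 0.35 and 0.42 at 25, 50 and 75% prevalence, with sensitivity 37–88% and specificity 44–93%. The plan states 0.33–0.41, 38–88% and 44–93%, which is close. The upper end reproduces (power 0.81 for 0.41 at 75% prevalence). The lower end, 0.33 at 50% prevalence, has power 0.75 at r = 0.6 and reaches 0.82 at r = 0.7. The calculation evidently uses all 70.

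**3. Patients without a computable ΔctDNA**, if the cited range applied here:
- 94% detection: 70 × 0.06 = 4.2, leaving 65.8, about 66
- 76% detection: 70 × 0.24 = 16.8, leaving 53.2, about 53

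**4. Power if those patients were excluded.** Exact two-sided Fisher power (point-probability version), holding effects that give about 80% at n = 70. Ranges reflect rounding of group sizes.

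| Prevalence | p1 vs p2 | r | n = 70 | n = 66 | n = 53 |
|---|---|---|---|---|---|
| 25% | 0.80 vs 0.40 | 0.50 | 0.80–0.82 | 0.81–0.83 | 0.66–0.69 |
| 50% | 0.77 vs 0.42 | 0.595 | 0.80 | 0.795 | 0.69–0.70 |
| 75% | 0.695 vs 0.295 | 0.595 | 0.81–0.82 | 0.79–0.82 | 0.67–0.69 |

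Power need not fall steadily with n, because the exact test is discrete. Setting r to 0.5 and 0.6 and re-solving the effects for 80% at n = 70 gives 0.78–0.82 at n = 66 and 0.64–0.70 at n = 53. The doubled-tail version at 75% prevalence, difference 0.41 and r = 0.6 gives 0.81, 0.77 and 0.66 at n = 70, 66 and 53.

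**5. Numbers needed to keep 70 computable values.** 70/0.94 = 74.5, so 75 response-evaluable patients; 70/0.76 = 92.1, so 93. At the plan's 70% evaluability: 74.5/0.70 = 106.4, so 107 enrolled; 92.1/0.70 = 131.6, so 132.

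**6. Instability near the detection limit (illustration only).** Assume independent Poisson counts of mutant molecules with the same mean at both visits, so no true change. An apparent fall of at least 30% then occurs with probability 0.23 at a mean of 10 molecules, 0.14 at 20 and 0.04 at 50. These means are assumptions; the article gives no molecule counts.

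**The case against.** Three stronger readings are tempting, and the article does not support them.

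*That patients with undetectable baselines are dropped.* No section says so. The article refers to prespecified reporting thresholds, promises to report the limit of detection and reproducibility, and announces missing-data handling. A rule for values below detection may stand in the unseen analysis plan. This objection stands: exclusion is what the stated definition implies if applied literally, not a rule the article sets.

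*That the stated 80% power is not met.* At 6% loss it is essentially met, and a clear shortfall appears only towards 24%. The detection range comes from other studies. This cohort is pretreated mCRPC tested with a 197-gene deep-sequencing panel, so its own rate is unknown and could be better.

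*That the concordance coprimary is underpowered.* The 80% belongs to a Fisher comparison of response rates. Concordance uses κ and correlation, for which no power is stated. The power statement also covers baseline markers, for which undetectable is a usable value, so the first coprimary outcome is untouched.

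It is also fair that the ≥30% decline is only exploratory. The asymmetry of percent change is no clear defect either: no correlation coefficient is named, and a rank coefficient or categorised κ would not be affected by skew.

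What the objection does not answer is that the article publishes percent change as the measure within a coprimary outcome. An analysis plan that used a log ratio or categories would depart from that definition, and one that kept percent change would still need a rule for zero baselines.

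**Conclusion.** The point holds in limited form. ΔctDNA as defined has no value at an undetectable baseline, is unstable just above the detection limit and cannot show newly emerging ctDNA. On the cited range this could affect about 4–17 of some 70 evaluable patients, selectively those with low burden, and the stated sample size does not allow for it.

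The effect on marker-change power is conditional on exclusion: near 80% with 66 patients, about 66–70% with 53 for the effects tabulated. This rests on three assumptions: that the cited detection range carries over to this assay and cohort, that undetectable baselines are as frequent among evaluable patients as overall, and that overall response is about 0.5–0.6. Neither actual exclusion nor a certain loss of power can be read from the article.

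**What to change.** Before ΔctDNA is analysed against response:

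1. Define ΔctDNA as log(on-treatment / baseline), with values below the limit of detection set to one fixed, prespecified value. Repeat the analysis with other substituted values as a sensitivity check.
2. For κ, use a complete two-category mapping that keeps every patient. Molecular nonprogression: undetectable at both visits, cleared, decreased, or stable within assay reproducibility. Molecular progression: increase beyond reproducibility, or newly detectable. Match this to RECIP nonprogression versus progression. Stable and increased must not share a category, because the boundary in Outcomes runs between stable disease and progression.
3. If percent change is kept, state that it applies only to patients with detectable baseline ctDNA, report how many are left out, and restate the marker-change power for about 53–66 patients.

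The cost is a change of definition, with no new samples or assays. The downside is slight dependence on the substituted value, which the sensitivity analyses would show. Timing matters: sample analysis began in January 2026, and a rule chosen after ctDNA has been compared with response would be open to the charge of being data-driven.
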